#### Sample size {14}

The sample size of this study is based on the primary endpoint. A 1.0 m/s difference in PWV is clinically relevant and can be expected with a magnesium intervention of 24 weeks in healthy subjects and a CKD population with accelerated CVD risk [11, 17]. Based on prior studies on arterial stiffness in populations with CKD stages 1–5, with mean PWV values between 10.5 and 12.0 m/s and a standard deviation (SD) of 1.4-3.5 m/s [10, 12, 13], we assume for our study population with an eGFR 15–50 ml/min/1.73m^2^ a SD of 2.0 m/s. With a statistical power of 80%, a two-sided significance of 0.05 and a rho of 0.7 to account for the correlation between baseline and follow-up measurements, 38 participants are required per group. To account for an anticipated drop-out rate of 15% during the 24 weeks, a total of 180 CKD patients will be included and randomized in a ratio of 1:1:1:1, with 45 participants in each intervention group. In case of an unexpected high drop-out rate (> 15%) for reasons not related to study participation (for example starting dialysis, transplantation, referral to a non-participating center), then additional participants can be recruited.

The sample size calculation was performed with the PASS 15.0.5 software and a statistical consultant.

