### Assignment of interventions: blinding

#### Who will be blinded {17a}

The randomized, double-blind design ensures that participants as well as the research team and care providers will be blinded for the magnesium citrate intervention. The magnesium citrate and placebo identification list will only be available to concerning research pharmacies. Randomization for the additional SFOH prescription is open-label and therefore known to all involved. Data analyses will be performed before revealing the randomization code.

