#### Plans to promote participant retention and complete follow-up {18b}

To promote participant retention and complete follow-up, contact through phone and email is encouraged and planning of visits are confirmed through email. Also, great effort is made to combine regular laboratory or physician hospital visits with research measurements to facilitate research investment. Participants who discontinue participation after the start of the intervention will be asked to accept the T3 PWV measurement to allow ITT analysis of the primary endpoint. Protocol deviations regarding the intervention will be handled in the analyses differentiating between ITT and on treatment analyses.

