### Statistical methods

#### Statistical methods for primary and secondary outcomes {20a}

Patient characteristics will be presented by treatment arm as mean ± standard deviation (SD) or median with an interquartile range (IQR) for normally and non-normally distributed continuous data, respectively. Categorical variables will be presented as number and percentage. Differences between treatment arms will be visually inspected for clinically relevant differences.

The primary and secondary endpoints will be analyzed with linear mixed models, with repeated measurements (at baseline, 12 weeks, and 24 weeks) and random intercepts at patient level. In case of non-normally distributed residuals of the outcome variables, suitable transformation (e.g., logarithmic) will be performed. Based on the −2 log likelihood evaluation, additional center level and random slopes will be added to the analysis when needed. The main analysis will focus on the three active intervention groups separately, in comparison to the placebo. Also, the additional value of the combined intervention of magnesium citrate and SFOH will be analyzed compared to solely magnesium citrate and SFOH supplementation by coding the magnesium citrate and SFOH as reference category, respectively. Due to stratified randomization, these important confounders are expected to be evenly distributed between the intervention groups. However, confounding by baseline differences of age, sex, eGFR, Kauppila index, baseline plasma magnesium, and phosphate concentrations will be considered in case of clinically relevant or ≥ 10% difference between groups. To evaluate when the effect of the intervention occurs at its maximum, an interaction term for both categorical time variables (12 and 24 weeks versus baseline) will be evaluated in the analysis for primary and secondary outcomes.

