The primary and secondary outcomes will be investigated as an ITT analysis. Within the ITT analyses, all participants will be included who have been randomized and participated in the baseline measurements and at least one follow-up visit. This analyses will be based on the initial treatment assignment and not on the treatment eventually received, thus not taking in to account dose alterations or cessation of (part of) the study intervention. Results will be considered statistically significant with a *P*<0.05 (2-sided) for the primary endpoint. For secondary endpoint analyses, we will mainly focus on effect estimates and confidence intervals. Data analysis will be performed in the SPSS 24.0 software for Windows (SPSS incorporated, Chicago, Il, USA) and StataSE 14 (StataCorp, College Station, USA) and will be performed blinded to treatment allocation.

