#### Methods in analysis to handle protocol non-adherence and any statistical methods to handle missing data {20c}

To evaluate the influence of non-adherence (treatment adherence < 80% based on pill-count), an on-treatment analysis will be performed in addition to the ITT analyses. Missing outcome variables will not be imputed since mixed models can handle these missing data. In case of missing data in relevant covariates, multiple imputation with predictive mean matching (PMM) will be performed.

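### The analysis labelled ITT requires a follow-up visit, so it is a modified ITT; baseline-only records could stay in the mixed model at no cost (minor)

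*Protocol article*

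**What the plan says.** All references are to the Protocol article.

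- **Statistical methods {20a}** labels the analysis of primary and secondary outcomes ITT, by initial assignment and regardless of dose changes or stopping. It then restricts who enters: "all participants will be included who have been randomized and participated in the baseline measurements and at least one follow-up visit".
- The same section analyses the endpoints with "linear mixed models, with repeated measurements (at baseline, 12 weeks, and 24 weeks) and random intercepts at patient level". Baseline PWV is therefore one of three modelled outcomes. The section does not say whether baseline means are arm-specific or shared.
- **Non-adherence and missing data {20c}**: "Missing outcome variables will not be imputed since mixed models can handle these missing data".
- **Retention {18b}**: participants who discontinue after starting the intervention "will be asked to accept the T3 PWV measurement to allow ITT analysis of the primary endpoint".
- **Blinding {17a}**: "Randomization for the additional SFOH prescription is open-label and therefore known to all involved".
- **Sample size {14}** supplies the planning values used below, including a 15% anticipated drop-out and 45 participants per arm.

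**The concern.** Membership of the primary set depends on something that happens after randomisation. Someone who leaves before any follow-up visit is removed, although a baseline PWV has been recorded and the model has a place for it.

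Likelihood-based handling of missing outcomes under missing at random works by using what was observed on those who leave. Removing their baseline values first gives up part of that protection. If leavers in one arm start with higher or lower PWV than those who stay, that arm's mean baseline among the retained is shifted. Regression to the mean then makes its average change look different even with no treatment effect.

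Arm-related early loss is conceivable here. Sucroferric oxyhydroxide (SFOH) is open label in two of four arms, the article expects gastro-intestinal effects from it, and PWV is first repeated at week 12.

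The qualifying visit is also loosely defined. PWV is measured at 12 and 24 weeks, whereas Adverse event reporting {22} mentions a questionnaire at 6 weeks. The text does not say whether a contact without PWV is enough to enter the set.

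**Working it through.** **1. Planning figures reproduce.** Inputs from Sample size {14}: difference 1.0 m/s, SD 2.0 m/s, and "With a statistical power of 80%, a two-sided significance of 0.05 and a rho of 0.7".

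- SD of change = 2.0 × √(2 × (1 − 0.7)) = 1.549 m/s.
- n per arm ≈ 2 × (1.960 + 0.842)² × 1.549² / 1.0² = 37.7, so 38. The article agrees: "38 participants are required per group".
- 38 / 0.85 = 44.7, so 45 per arm and 4 × 45 = 180.

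SD 2.0 and rho 0.7 are therefore fair inputs for the next steps.

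**2. How many could be excluded.** 15% of 45 is 6.75 per arm, and 15% of 180 is 27. At the planned rate this is a ceiling, reached only if every drop-out leaves before any follow-up visit.

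**3. Bias formula.** Take arm-specific baseline means, no true effect, equal correlation rho between visits, and early loss that depends on baseline PWV. Let s be the retained group's mean baseline minus that of the whole arm, in SD units.

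- Bias in an arm's mean change when leavers are excluded = (rho − 1) × SD × s = −0.3 × 2.0 × s = −0.6 s.
- Bias in the contrast = −0.6 × (s_active − s_control).
- If baseline-only records are kept, maximum likelihood moves the week-24 mean by rho times the baseline shift and this term cancels.

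**4. Numbers.** The article gives only an overall drop-out rate, so the early-loss rates and their link to baseline are assumptions. Here the odds of early loss rise 2.7-fold per SD of baseline PWV in any arm with loss. The value of s comes from integrating this logistic loss model over a normal baseline.

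| Early loss, control vs active | s control | s active | Bias by formula (m/s) | Simulated bias, excluded (m/s) |
|---|---|---|---|---|
| 0% vs 11% | 0 | −0.103 | 0.062 | 0.062 |
| 3% vs 7% | −0.029 | −0.065 | 0.022 | 0.020 |
| 5% vs 10% | −0.047 | −0.091 | 0.026 | 0.024 |
| 7% vs 7% | −0.065 | −0.065 | 0 | 0 |

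With a weaker link (1.5-fold per SD), 3% vs 7% gives about 0.01 m/s.

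For 0% vs 11%, keeping the baseline-only records gave a simulated bias of 0.0005 m/s. The SD of the estimate was 0.337 whether they were kept or excluded. Type I error with exclusion was 5.3%.

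**5. An extreme case.** With 5% loss in control, unrelated to baseline, and 22% baseline-dependent loss in the active arm at a steeper slope, the bias was 0.155 m/s excluded and 0.006 m/s kept. Type I error was 7.3% and 4.9%.

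**6. Where the exclusion does not matter, or keeping does not help** (20,000 simulated two-arm comparisons per mechanism).

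- Loss completely at random: no bias either way.
- Baseline means constrained equal across arms, under the extreme case in step 5: 0.006 m/s either way.
- Loss driven by the unseen week-24 value: −0.155 m/s excluded and −0.259 m/s kept.

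**The case against.** The strongest reply is that this is a disclosed, prespecified modified-ITT rule with little numerical effect.

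- **Few people are affected.** Stopping treatment does not remove anyone, and the request for a T3 PWV after discontinuation restores membership with one visit. Only those who decline every later visit drop out of the set, probably well under 15%. This stands, and it limits the size of the problem without changing the rule.
- **Realistic bias is small.** At 3% vs 7% it is about 2% of the 1.0 m/s target. The 0.155 m/s case needs 22% loss before any follow-up in one arm, which is more than the 15% the article expects for all drop-out. This stands.
- **It depends on the model form.** With a common baseline mean the two analyses agree. This stands; the article does not state the form.
- **A baseline-only participant has no observed change and adds no precision.** True, but the reason to keep the record is to avoid bias.

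Three stronger readings are tempting, and the document does not support them.

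1. A reader might infer that the rule contradicts {20c}. It does not: participants with baseline and one follow-up PWV still have a missing outcome for the model to handle, so both statements can be carried out. They fit poorly together, no more.
2. A reader might infer that open-label SFOH makes bias likely. Nothing in the article links intolerance of SFOH to baseline PWV, and intolerance leads to stopping treatment more directly than to leaving the study.
3. A reader might infer that keeping everyone cures drop-out bias. Step 6 shows a case where it does not.

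**Conclusion.** The point holds as a minor one. The set is a modified ITT labelled ITT, and it discards usable records from a model that could include them.

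The possible bias in the 24-week contrast is about 0.02 m/s at 3% vs 7% early loss and about 0.06 m/s at 0% vs 11%, against a target for which the article says "A 1.0 m/s difference in PWV is clinically relevant". These figures need all of the following: arm-specific baseline means, early loss that differs by arm, loss related to baseline PWV (assumed 2.7-fold odds per SD), SD 2.0 m/s and rho 0.7. If early loss is alike in both arms, or baseline means are constrained equal, there is no bias to remove. The sample size is unaffected.

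**What to change.** In Statistical methods {20a}:

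- Define the primary set as all randomised participants, analysed as randomised, with every available PWV value (baseline, 12 and 24 weeks) in the mixed model, including participants with baseline only.
- State whether the model uses arm-specific or common baseline means.
- Report by arm the number without any follow-up PWV.
- Keep the restricted set as a sensitivity analysis, name it modified ITT, and require at least one follow-up PWV measurement in place of an undefined visit.
- Say that this handles loss explained by observed PWV only. Loss driven by unobserved outcomes would need its own sensitivity analysis.

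The cost is a few sentences. It needs no new data and no change in sample size, and the simulated SD of the estimate was the same either way.

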#### Interim analyses {21b}

No interim analyses will be performed. However, halfway study recruitment a recalculation of the sample size will be performed based on the PWV SD, rho, and percentage of dropout until then, with adjustment of the sample size if applicable.

#### Methods for additional analyses (e.g., subgroup analyses) {20b}

The intervention effect on plasma magnesium and phosphate and their urinary excretion will be analyzed with linear mixed models with repeated measurements and linear regression analysis, respectively. Subgroup sensitivity analyses will be reported for the stratified eGFR, Kauppila index, sex, median age, blood pressure, presence of diabetes, median baseline magnesium, and phosphate levels and proton pump inhibitor or diuretic use to test the robustness of the analysis. In addition, for the primary endpoint of PWV, the mediating effect by plasma magnesium and phosphate levels, blood pressure, T_50-_test, CPPs, α-klotho, and cFGF-23 will be explored using causal mediation analysis.

The analysis of the explorative ^18^F-NaF and ^18^F-FDG PET-scans will be based on the axial regions of interest (ROI). Differences between the intervention groups in standardized uptake value (SUV), target to background ratio (TBR), and most diseased segment (MDS) will be analyzed with linear regression analysis, with adjustment for baseline value.

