#### Strategies to improve adherence to interventions {11c}

Medication intake, tolerability, and adherence is actively assessed during each study visit. Pill count will be performed at 12 and 24 weeks of intervention. Subjects will be considered compliant based on pill count when they take at least 80% of the study medication. In addition to plasma levels of magnesium and phosphate, also 24-h urinary magnesium and phosphate concentrations at baseline and after 24 weeks of intervention will be supportive in the evaluation of adherence.

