Secondary endpoints include the difference in calcification propensity (T_50-_test), (secondary) CPP concentrations and the difference in serum/plasma concentrations of α-Klotho, C-terminal (c)FGF23, hsCRP, phosphate, and magnesium, over 24 weeks between groups. All measurements are performed in samples collected after at least 3 h of fasting. Serum for the T_50-_test and the gel filtration method based quantification of CPP measurements is frozen at − 80 °C and will be measured as described previously [24, 50]. The T_50-_test established inter-assay coefficients of variation of standards precipitating at 120, 260, and 390 min are 7.8%, 5.1%, and 5.9%, respectively [24]. These measurements will be performed as one batch without additional freeze-thaw. EDTA-plasma concentrations of cFGF23 and iPTH, and serum α-Klotho are centrally measured at the Amsterdam UMC, after storage at -80 °C at participating sites. Routine blood tests are performed directly after withdraw at the laboratories of participating centers, including plasma magnesium, phosphate, creatinine, hsCRP, calcium, albumin, potassium, hemoglobin, ferritin, lipid spectrum (low density lipoprotein (LDL), high density lipoprotein (HDL), total cholesterol and triglycerides), fasting glucose, and bicarbonate. The eGFR is calculated using the creatinine based CKD-EPI (Chronic Kidney Disease Epidemiology Collaboration) equation and plasma calcium is corrected for albumin concentration [calcium _mmol/L_ + 0.016 × (40 – albumin _g/L_)]. In addition, urinary magnesium, phosphate, creatinine, sodium, and protein are determined in 24-h urine samples at baseline and at 24 weeks of intervention. Additional parameters include demographic characteristics, anthropometric measurements, and medical history at baseline. Also seated blood pressure measurements are performed at baseline and 12 and 24 weeks with an oscillometric, automatic blood pressure monitor averaging a second and third measurement. An overview of all study measurements and procedures are presented in Table 2.

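### The regression for 24-h urinary magnesium and phosphate excretion states no baseline term, although baseline urine is collected and the PET regressions in the same section are baseline-adjusted

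*Protocol article*

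**What the plan says.** The Protocol article, Methods for additional analyses {20b}, covers the intervention effect on plasma magnesium and phosphate and then adds: "and their urinary excretion will be analyzed with linear mixed models with repeated measurements and linear regression analysis, respectively". Read with the closing word, plasma levels get mixed models and urinary excretion gets linear regression. The sentence does not say whether the urinary outcome is the week-24 value or the change from baseline, and it lists no covariates.

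The next paragraph of {20b} says that the PET measures "will be analyzed with linear regression analysis, with adjustment for baseline value".

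Outcomes {12} fixes the urine sampling: "urinary magnesium, phosphate, creatinine, sodium, and protein are determined in 24-h urine samples at baseline and at 24 weeks of intervention". Strategies to improve adherence {11c} gives the purpose: the urinary measures "will be supportive in the evaluation of adherence", in addition to plasma levels and alongside pill count.

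The only covariate rule elsewhere is in Statistical methods {20a}. It concerns the primary and secondary endpoints, applies only when the groups differ at baseline, and lists baseline plasma magnesium and phosphate but no urinary value. No section supplies a baseline term for urinary excretion.

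**The concern.** In each participant the urinary measures have one baseline and one week-24 value. The plan has two analyses of this before-and-after kind fitted by linear regression. It writes the baseline term for PET, an exploratory analysis in 40 participants, and does not write it for urine, which is collected in the whole trial.

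A plain regression of week-24 excretion on arm would leave a collected prognostic value unused. Between-person variation that baseline could explain would stay in the residual, and part of any chance baseline difference between arms would pass into the estimated effect. A regression of the change score would use the baseline but with a fixed weight of one, which is less efficient than letting the data set the weight. On either reading, stating the baseline covariate improves the analysis.

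At stake is the precision of one of the supportive checks on exposure to treatment. The primary result on pulse wave velocity (PWV) does not depend on it.

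**Working it through.** **Inputs from the document.** Urine at baseline and 24 weeks ({12}, {11c}); linear regression with no stated covariate ({20b}); 38 per group, SD 2.0 m/s, difference 1.0 m/s, rho 0.7, 80% power and two-sided 0.05 for PWV ({14}). No effect size, SD, rho or power is given for urine.

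**The plan's own figure.** {14} states: "The sample size of this study is based on the primary endpoint". Take n per group = 2 × (1.96 + 0.842)² × SD² / difference², where 2 × (1.96 + 0.842)² ≈ 15.70.
- Change score: SD² = 2.0² × 2 × (1 − 0.7) = 2.40, so n = 15.70 × 2.40 / 1.0² = 37.7, rounded up to 38. Then 38 / 0.85 = 44.7, rounded up to 45, and 4 × 45 = 180. This matches the plan.
- Baseline as covariate: SD² = 4 × (1 − 0.49) = 2.04, so n = 33.
- No use of baseline: SD² = 4, so n = 63.

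The PWV sizing is therefore consistent with a change-score variance. That bears on how the silent urinary sentence might be read, but it gives no figure for urine.

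**Precision for urine.** Assume equal SD (σ) at baseline and week 24 and a common correlation rho. The residual variances are:
- week-24 value, unadjusted: σ²
- change score: 2σ²(1 − rho)
- week-24 value with baseline as covariate: σ²(1 − rho²)

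Confidence-interval width scales with the square root. Ignoring the single degree of freedom used by the covariate, the ratio of adjusted to unadjusted width is √(1 − rho²). The ratio of adjusted to change-score width is √[(1 − rho²) / (2(1 − rho))] = √[(1 + rho)/2].

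| rho (assumed) | √(1 − rho²) | Narrower than unadjusted week 24 | √[(1 + rho)/2] | Narrower than change score |
|---|---|---|---|---|
| 0.3 | 0.954 | about 5% | 0.806 | about 19% |
| 0.5 | 0.866 | about 13% | 0.866 | about 13% |
| 0.7 | 0.714 | about 29% | 0.922 | about 8% |

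The 0.7 row borrows the PWV value; nothing in the document says that it holds for urine.

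**Chance imbalance.** Under the same assumptions, a chance baseline difference D between two arms shifts the unadjusted week-24 contrast by rho × D and the change-score contrast by −(1 − rho) × D on average. Covariate adjustment removes both shifts.

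**The case against.** The strongest reply is that silence is not exclusion. The sentence in {20b} names a type of model for an additional analysis. A journal article may leave covariates to the full protocol or the analysis plan, which are not shown. A change score is also a natural reading: the primary endpoint is defined as a difference in change, and the PWV sample size reproduces with a change-score variance. A change score does use the baseline.

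Much of this stands. A reader might infer that the plan compares week-24 excretion while deliberately ignoring baseline; the text does not say so. What remains is that the section goes as far as naming the model, spells out the baseline term for PET in the next paragraph, and leaves it out here. The change-score reading does not remove the gain, as the last column of the table shows.

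A reader might also put the loss at about 10 power points. That figure needs two choices which the document does not make: rho = 0.5, and a true effect that gives exactly 80% power unadjusted. From that 80%, adjustment gives 83.6%, 89.9% and 97.5% at rho 0.3, 0.5 and 0.7. If unadjusted power were already 99%, the gain would be at most about 1 point. Over rho 0.2 to 0.8 and different starting powers, the loss runs from under 1 to about 41 points. No power is planned for urine, so a single headline figure is unsupported and interval width is the better measure.

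Finally, urine might be taken as the one objective check that treatment was taken. {11c} calls it supportive. Plasma magnesium and phosphate are secondary endpoints with their own mixed models, and the on-treatment analysis in {20c} rests on pill count.

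**Conclusion.** The point holds as a minor clarification. {20b} specifies the urinary regression without stating a baseline term, although the baseline value is collected and the PET regressions in the same section are adjusted for it. Adding the term is a gain in precision on either reading of the outcome: intervals about 5% to 29% narrower than an unadjusted week-24 comparison, or about 19% to 8% narrower than a change score, as rho goes from 0.3 to 0.7. These ranges rest on assumed correlations, equal SDs at the two visits and a linear relation with baseline. The document does not show that baseline is excluded, that any planned power is lost, or that the interpretation of the PWV result hangs on this analysis.

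**What to change.** In {20b}, extend the urinary sentence with the provision already used for PET, so that week-24 24-h excretion of magnesium and of phosphate is each regressed on arm with the baseline excretion of the same analyte as covariate.

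The cost is one phrase; no new data or visits are needed. The only downside is that a participant without a baseline urine value needs that covariate imputed, and {20c} already plans multiple imputation with predictive mean matching for missing relevant covariates. If the full protocol or analysis plan already contains the baseline term, it is enough to confirm that the article's wording is shorthand for it.
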